### Statistical analyses

Baseline data will be presented comparing the two treatment groups.

All analyses will be on an intention-to-treat basis. Differences between the stepped-care group and the usual care group will be tested using mixed model analyses. To test the cumulative incidence of depression over time, logistic mixed model analysis will be used. The obtained odds ratio describes the reduction in the risk of a MINI/DSM-IV depressive disorder in the intervention group relative to the control group. Linear and logistic mixed models (depending on the outcome) will also be used to test differences in symptoms of depression and anxiety and quality of life between both groups over time. If necessary, the models will be adjusted for confounders.

Sub group analyses will be performed to check for an interaction effect between depression severity at baseline and improvement in depressive symptoms at 12 months.

In case of unequal distributions of demographic variables between the two treatment groups, multivariate analyses techniques will be used to correct for these differences.

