### Outcomes

The primary clinical outcome is the cumulative incidence of DSM-IV major depressive disorder after 12 months according to the Mini International Neuropsychiatric Interview (MINI) [33,37]. The MINI will be administered by telephone at baseline and after 6 and 12 months after baseline by qualified research assistants.

Depression severity will be measured using the PHQ-9 [32,44]. The PHQ-9 is a widely used validated instrument to measure depression symptoms in general practice.

Quality of life will be measured using the EuroQol (EQ-5D) [45]). The obtained EQ-5D scores will be used to calculate utilities according to the Dutch tariff. QALYs will be calculated using the area-under-the-curve method with linear interpolation between time points.

For the economic evaluation, costs will be measured using the TiC-P questionnaire [46]. Costs that will be included are costs for healthcare utilization, informal care, and work absenteeism and presenteeism. Medication use will be retrieved from the patient’s pharmacy. If available, Dutch guideline prices will be used to value resource use. Medication use will be valued using prices of the Royal Dutch Society for Pharmacy. Lost productivity costs will be calculated according to the friction cost approach (friction period 154 days) using the mean age- and sex-specific income of the Dutch population. According to the friction cost approach a sick employee is replaced after a certain amount of time (the friction period) after which there are no lost productivity costs anymore. All costs will be adjusted to the year in which most data is collected using consumer price indices.

All secondary outcomes mentioned above will be administered at baseline, 3, 6, 9 and 12 months after inclusion through web-based questionnaires. If patients do not have access to the internet or prefer hard copies, we will provide these. In the intervention group, the PHQ-9 will also be administered by the nurse in the general practice for clinical monitoring and adjusting treatment when necessary.

Other secondary clinical outcomes include blood pressure, low-density lipoprotein (LDL) cholesterol and glycosylated haemoglobin (HbA1C). These outcomes will be measured at baseline and at 12 months follow-up and are performed as part of the usual care for this group of patients. Therefore, patients do not undergo any extra physical measurements.

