### Sample size

The trial is powered to detect a difference of 15% in the cumulative incidence rates of MINI/DSM-IV depressive disorder between the conditions after 1 year. The incidence rate is expected to be 30% in the usual care group and 15% in the intervention group based on findings from earlier studies [2,25,26]. Using a standard sample size calculation, 121 patients per group are needed, assuming a power of 0.8 and an alpha of 0.05. However, we need to correct for the fact that there is a multilevel setting with three levels: GPs, patients and measurements. Therefore we have first adjusted for the fact that we do not have one, but multiple measurements per patient. Assuming these measurements are clustered with an intraclass correlation (ICC) of 0.45, seventy-one patients per group are needed. Subsequently, we adjusted this figure further for clustering of patients within GP practices. Assuming an ICC of 0.05 for clustering of patients within the 30 GP practices, we need a total of 177 patients. Finally, we adjusted for a dropout rate of 25%, which means that 236 patients (118 patients per group) need to be included in this trial. This power calculation is based on the method described by Twisk in 2006 [55].

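### The primary odds ratio is described as a reduction in risk, which is wrong for an outcome expected in 15% to 30% of patients

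*Protocol article*

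**What the plan says.** The Outcomes section of the protocol article defines the endpoint: "The primary clinical outcome is the cumulative incidence of DSM-IV major depressive disorder after 12 months". It is measured by the MINI, on this schedule: "The MINI will be administered by telephone at baseline and after 6 and 12 months after baseline by qualified research assistants". Table 1 agrees.

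The Sample size section works on the absolute scale: "The trial is powered to detect a difference of 15% in the cumulative incidence rates of MINI/DSM-IV depressive disorder between the conditions after 1 year", with the assumption "The incidence rate is expected to be 30% in the usual care group and 15% in the intervention group". It also says that "there is a multilevel setting with three levels: GPs, patients and measurements".

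The Statistical analyses section then states: "To test the cumulative incidence of depression over time, logistic mixed model analysis will be used". The next sentence interprets the result: "The obtained odds ratio describes the reduction in the risk of a MINI/DSM-IV depressive disorder in the intervention group relative to the control group".

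The section does not give the outcome coding (ever depressed, or current status at each visit), the random effects, or whether the treatment contrast is taken at 12 months or averaged over visits. It describes no conversion of the odds ratio to a risk scale.

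**The concern.** The interpretive sentence is a positive statement about the primary result, and at these incidences it is incorrect. For any protective effect on a common outcome, one minus the odds ratio exceeds one minus the risk ratio. The Background cites earlier stepped-care programmes in terms of relative risk (up to a 50% reduction), so readers would compare the trial's figure with numbers on a different scale and find it more favourable than it is.

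A second issue lies behind the first. A three-level structure of practices, patients and measurements suggests a patient random intercept, which moves the odds ratio further from 1 for the same risks. Cumulative incidence is also absorbing: a patient who is a case at 6 months remains one at 12. A patient-intercept model on rows coded that way is badly behaved. If the rows record current status instead, the model estimates point prevalence, which is not the endpoint in the Outcomes section.

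**Working it through.** **Inputs from the document.** Risks 30% and 15%; power 0.80; alpha 0.05 (two-sided reproduces the figure); within-patient ICC 0.45; practice ICC 0.05; 30 practices; dropout 25%; MINI after baseline at 6 and 12 months. The Intervention section also mentions MINI criteria at 3 and 9 months. I follow Outcomes and Table 1.

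**1. The plan's own figures.**
- n = [1.960·√(2·0.225·0.775) + 0.842·√(0.30·0.70 + 0.15·0.85)]² / 0.15² = 120.5, so 121 per group, as stated ("121 patients per group are needed, assuming a power of 0.8 and an alpha of 0.05").
- Repeated measures: 121·(1 + 3·0.45)/4 = 71.09. The stated 71 needs four measurements per patient.
- Clustering: solve M = 142.2·(1 + (M/30 − 1)·0.05), giving M = 177.0.
- Dropout: 177/0.75 = 236.

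The chain reproduces, so the point does not rest on an arithmetic error.

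**2. Odds ratio against risk ratio at the planned rates.**
- Risk ratio = 0.15/0.30 = 0.50; difference 15 points.
- Odds ratio = (0.15/0.85)/(0.30/0.70) = 0.412, read as a 59% reduction.
- Conversely, an odds ratio of 0.50 at 30% control risk gives treated odds 0.5·0.4286 = 0.2143, risk 17.6% and risk ratio 0.588. That is a 41% reduction, not 50%.

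**3. With a random intercept.** Assumption: the ICC is on the latent scale, so SD = √[ICC/(1 − ICC)·π²/3]. Marginal risks are held at 30% and 15%, integrating numerically over a normal intercept.

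| ICC | SD | Conditional odds ratio | Read as |
|---|---|---|---|
| 0.05 | 0.42 | 0.40 | 60% |
| 0.20 | 0.91 | 0.37 | 63% |
| 0.45 | 1.64 | 0.29 | 71% |
| 0.60 | 2.22 | 0.23 | 77% |

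The usual approximation agrees at ICC 0.45: exp[ln(0.412)·√(1 + 0.346·2.69)] = 0.29.

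**4. Patient intercept on cumulatively coded rows.** This needs 6-month incidences, which the document does not give. Assumption: constant control hazard, and no effect during the three-month watchful-waiting step.
- Control: 1 − 0.70^0.5 = 16.3%.
- Intervention: survival to 3 months 0.70^0.25 = 0.915; to 6 months 0.915·(0.85/0.915)^(1/3) = 0.893; incidence 10.7%.
- Only the patterns (0,0), (0,1) and (1,1) can occur.
- Large-sample maximum likelihood without a time effect: SD about 5.4, odds ratio 0.08.
- With a time effect, minus log-likelihood (summed over the two groups) falls from 1.367 at SD 6 to 1.348 at SD 10 and about 1.343 at SD 20, and is still edging down at SD 40. The odds ratio is 0.06 at SD 6 and about 0.0001 at SD 20. No finite maximum was found.

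**5. Other models that fit the same words, on the same assumed incidences.**
- Crude odds ratio pooled over both visits: mean risks 23.2% and 12.9%, giving 0.49.
- Rows that stop at the first positive MINI, no patient effect: event proportions 0.300/1.837 = 0.163 and 0.150/1.893 = 0.079, giving 0.44. Nothing diverges.

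**6. What one outcome per patient does to the sample size, by the plan's own method.**
- One measurement: M = 242·(1 + (M/30 − 1)·0.05) = 385, or about 514 after dropout.
- Two measurements: 121·1.45/2 = 87.7 per group, about 236 before dropout and 314 after.
- With 177 analysed and one outcome each: design effect 1 + (5.9 − 1)·0.05 = 1.245; effective n = 88.5/1.245 = 71.1 per group; z = [0.15 − 1.960·√(0.34875/71.1)]/√(0.3375/71.1) = 0.18; power about 57%.

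**The case against.** The best defence is that the article names only a class of model. Random effects and outcome coding are commonly left to an analysis plan, and none is shown. The three levels appear in the sample-size reasoning, not in a model specification. Two ordinary logistic mixed models fit the stated aim and avoid the breakdown in step 4: one ever-depressed indicator per patient with a practice intercept, or a discrete-time model whose rows stop at the first event. Sizing a trial on a difference in proportions and analysing it by logistic regression is routine. All of this stands, and it makes steps 3 and 4 conditional.

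Three stronger conclusions might be inferred, and the document does not support them. One is that the planned model cannot estimate 12-month cumulative incidence. The article says that this is what is tested, and suitable codings exist. Another is that the effect will be overstated whatever is done. An odds ratio reported as an odds ratio overstates nothing, and averaging a delayed effect over both visits could give about 0.49, close to the true risk ratio. That figure is a crude one without a patient effect, so it offers no general protection. The third is that the significance test is invalid. How the estimate is described does not affect the test.

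The defence does not reach the interpretive sentence, which is in the text and is wrong at the plan's own rates.

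**Conclusion.** The point holds for the interpretation of the primary result. At the planned 30% and 15%, reading the odds ratio as a risk reduction turns 50% into 59%; this uses only the document's figures. With a patient random intercept it becomes about 71%, if ICC 0.45 is latent-scale (60% to 77% over ICC 0.05 to 0.60).

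The degenerate fit (odds ratio 0.08, or no finite maximum found) requires a patient intercept, cumulatively coded rows and the assumed 6-month incidences together. The drift to point prevalence requires current-status coding. The article neither adopts nor excludes these structures, so they are reasons to fix the contrast before analysis. They do not show that the analysis will fail.

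**What to change.** 1. Reword the sentence so that the odds ratio is called an odds ratio and not a reduction in risk.
2. State that the primary contrast is ever MINI-positive by 12 months (6- or 12-month MINI), one outcome per patient, with a random effect for the randomised cluster and no patient intercept on cumulative rows. A discrete-time model whose rows stop at the first event, with the same cluster term, is an acceptable alternative and uses patients who have the 6-month but not the 12-month MINI.
3. Report the 12-month risk difference and risk ratio with 95% confidence intervals by standardisation, with the odds ratio as supplementary. The result is then on the scale used to size the trial.

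No new data or visits are required. The cost is in the power statement. The reduction from 121 to 71 per group relies on four measurements per patient, whereas the MINI has two after baseline and the redefined outcome only one. The stated 80% power at 236 then no longer follows: the same method gives about 57% at 236, or about 514 patients for 80%. The sponsor should restate the power openly alongside the change.

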#### Economic evaluation

Both a cost-effectiveness analysis and a cost-utility analysis will be performed. Missing cost and effect data will be imputed using multiple imputation according to the MICE algorithm developed by Van Buuren [56]. The results of the imputed datasets will be pooled using Rubin’s rules [57]. Costs typically have a highly skewed distribution. Policy makers want to have information on the difference in mean total costs between the two treatment groups in order to be able to estimate the total health care budget needed for a specific condition [58]. Therefore, bias-corrected and accelerated bootstrapping with 5000 replications will be used to estimate 95% confidence intervals around the mean difference in total costs between the treatment groups. Incremental cost-effectiveness ratios (ICERs) will be calculated by dividing the difference in mean total costs between the treatment groups, by the difference in mean effects between the treatment groups. Bootstrapping will also be used to estimate the uncertainty surrounding the ICERs, which will be graphically presented on cost-effectiveness planes. Cost- effectiveness acceptability curves will be estimated as well. Cost-effectiveness acceptability curves show the probability that the stepped-care program is cost-effective in comparison with usual care for a range of different ceiling ratios (i.e. the willingness to pay for 1 extra recovered patient), thereby showing decision uncertainty [59].

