## Methods/design

### Design

An economic evaluation from a societal perspective will be performed alongside a multi-center, cluster randomized controlled trial with a one year follow up.

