### Setting

The study will be carried out in approximately thirty general practices in the Netherlands. To select these practices, we will make use of the Academic Network of General Practitioners (GPs) of the Department of General practice and of the VU medical centre.

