### Randomization

Randomization will be done at the level of the participating practice nurses to avoid contamination between the treatment groups and will be performed by a statistician blinded to characteristics of the general practices using a computer generated list of random numbers. Before patients are recruited, participating practices will be randomly allocated to serve as intervention practices where the stepped-care treatment will be implemented, and control practices where care as usual will be given. Patients will be allocated to either one of the treatment conditions, based on the general practice where they are registered. Blinding of patients, GPs and practice nurses is not possible due to the nature of the intervention.

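### The economic analysis of this cluster-randomised trial is specified without a practice level, so cost uncertainty is understated if patients are resampled individually and costs cluster by practice

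*Protocol article*

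**What the plan says.** The Design section places the economic evaluation "alongside a multi-center, cluster randomized controlled trial with a one year follow up". Under Randomization, "Randomization will be done at the level of the participating practice nurses", and patients take the arm of the practice where they are registered. Under Setting, "The study will be carried out in approximately thirty general practices in the Netherlands".

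The Sample size section acknowledges the resulting structure of practices, patients and measurements and inflates for it: "Assuming an ICC of 0.05 for clustering of patients within the 30 GP practices, we need a total of 177 patients". The Statistical analyses section proposes mixed models for the incidence of depression, for symptoms of depression and anxiety, and for quality of life. It does not mention costs.

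The Economic evaluation section sets out its own procedure:

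- Imputation: "Missing cost and effect data will be imputed using multiple imputation according to the MICE algorithm", pooled with Rubin's rules.
- Cost difference: "bias-corrected and accelerated bootstrapping with 5000 replications will be used to estimate 95% confidence intervals around the mean difference in total costs". The reason given for the bootstrap is the skewness of costs.
- ICER: the difference in mean costs divided by the difference in mean effects.
- Uncertainty of the ICER: a bootstrap shown on cost-effectiveness planes, plus acceptability curves.

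None of these steps refers to the practice or the nurse, and the unit that is resampled is not named.

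**The concern.** Patients of one practice share a nurse, GPs and an allocation. If their costs or effects are correlated, the variance of a difference between arms has a between-practice part. A bootstrap that draws patients one at a time does not reproduce that part. BCa limits correct for bias and skewness and do not restore it.

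The matter is not peripheral. Cost-effectiveness is in the title and is the stated aim, and the acceptability curve is the display meant to convey decision uncertainty. If the variance is understated, the probability that the program is cost-effective is pushed too far from one half, in whichever direction the point estimate lies.

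The design gives some reason to expect correlation in costs. In each intervention practice the nurse acts as care manager and generates the visits, telephone contacts, problem-solving sessions and GP referrals. On the effect side, the protocol itself assumes an ICC of 0.05 for the incidence of depression.

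**Working it through.** **Inputs.** From Setting and Sample size: about 30 practices; ICC 0.05 within practices for the clinical outcome; 177 patients before and 236 after the allowance for 25% dropout. An equal split into about 15 practices per arm is assumed. The protocol gives no ICC for costs, so a range of 0.01 to 0.10 is used.

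**The plan's own figures.** "The incidence rate is expected to be 30% in the usual care group and 15% in the intervention group", and from this "121 patients per group are needed, assuming a power of 0.8 and an alpha of 0.05".

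- Two proportions, two-sided 0.05, power 0.80, pooled variance under the null: 121 per group.
- Repeated measurements, ICC 0.45, four measurements: 121 × (1 + 3 × 0.45)/4 = 71.1, so 71 per group and 142 in total.
- Clustering in 30 practices: 142 × (1 − 0.05)/(1 − 142 × 0.05/30) = 176.7, so 177.
- Dropout: 177/0.75 = 236.

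The chain reproduces. The practice step equals a design effect of 1 + (5.9 − 1) × 0.05 = 1.245, where 5.9 = 177/30. So the plan treats practice clustering as worth about 25% more patients for the clinical outcome.

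**Effect on the cost interval if patients are resampled individually.** With m patients per practice:

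- design effect DE = 1 + (m − 1) × ICC
- interval too narrow by 1 − 1/√DE
- true coverage of a nominal 95% interval = 2Φ(1.96/√DE) − 1

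Two values of m bracket the case: 177/30 = 5.9, and 236/30 = 7.87 because the imputation brings all included patients into the analysis. Example at ICC 0.05 and m = 5.9: √1.245 = 1.116; 1 − 1/1.116 = 10.4%; coverage 2Φ(1.96/1.116) − 1 = 92.1%.

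| Assumed cost ICC | m | DE | √DE | Too narrow by | Coverage |
|---|---|---|---|---|---|
| 0.01 | 5.9 | 1.049 | 1.024 | 2.4% | 94.4% |
| 0.01 | 7.87 | 1.069 | 1.034 | 3.3% | 94.2% |
| 0.05 | 5.9 | 1.245 | 1.116 | 10.4% | 92.1% |
| 0.05 | 7.87 | 1.343 | 1.159 | 13.7% | 90.9% |
| 0.10 | 5.9 | 1.490 | 1.221 | 18.1% | 89.2% |
| 0.10 | 7.87 | 1.687 | 1.299 | 23.0% | 86.9% |

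**Simulation as a rough check.** Skewed (gamma) costs, 30 practices of unequal size, 236 patients, 1500 runs, percentile intervals:

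| Cost ICC | Patients resampled | Practices resampled |
|---|---|---|
| 0 | 93.9% | 92.6% |
| 0.01 | 93.1% | 91.7% |
| 0.05 | 87.7% | 91.3% |
| 0.10 | 82.7% | 91.9% |

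Coverage with patients resampled falls as the ICC rises; with practices resampled it is roughly level but still below 95%. About 15 clusters per arm are too few for a plain cluster bootstrap to reach its nominal level. The plan specifies BCa rather than percentile intervals, so the table shows the direction and the small-cluster problem; its percentages are not estimates for the plan.

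**The case against.** The strongest reply is that the section is silent rather than wrong. BCa is a type of interval and can be applied to resampled practices; MICE is an algorithm and its imputation model may include practice. The article condenses a fuller protocol, and the resampling unit is a detail that such an article may leave out. This stands in part: it is not established that patients will be resampled individually. But the section is not merely brief. It names the interval type, the number of replications, the imputation algorithm, the pooling rule and the quantity compared, and it justifies the bootstrap by skewness alone. Followed in the usual way, that text gives an analysis of independent patients.

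A second reply is that the general opening sentence on mixed models under Statistical analyses also covers costs. It does not, because the Economic evaluation section names a different method for costs and ICERs.

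Other replies do limit the point:

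- A reader might infer that the intervals are bound to be too narrow. That needs both individual resampling and a positive ICC. At a cost ICC of 0.01 the loss is only 2–3%.
- A reader might infer that costs cluster at least as strongly as the diagnosis. The documents give no figure, and total costs include informal care and lost productivity, which need not follow the practice.
- A reader might infer that confidence intervals for the ICER are affected. None is announced: BCa limits are named for the cost difference only, and ICER uncertainty is shown on planes and through acceptability curves.
- The simulations used percentile limits and fell slightly short of 95% even at ICC 0, so not all of the shortfall in them comes from clustering.

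**Conclusion.** The point holds in conditional form. The method for the trial's main question is written without the unit of randomisation, although the same document corrects its sample size for that unit. If patients are resampled individually and the cost ICC equals the protocol's clinical value of 0.05, the cost-difference interval is 10–14% too narrow and covers about 91–92%. Over ICCs of 0.01 to 0.10 the shortfall in width runs from about 2% to 23%, with coverage from about 94% down to 87%. The planes and acceptability curves would overstate certainty in the same direction.

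This rests on three assumptions: individual resampling, a cost ICC that the documents do not supply, and roughly equal practices split evenly between the arms. The consequence of an imputation model without practice cannot be quantified from the documents. The randomisation, the stated sample size chain and the quantity being estimated are not affected.

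**What to change.** In the Economic evaluation section, replace the unspecified bootstrap with one that respects the unit of randomisation. Either of these would do:

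1. A two-stage bootstrap within arm: resample practices, then patients within practices, with a small-sample correction because there are only about 15 clusters per arm.
2. A bivariate mixed model for costs and effects with a practice random intercept.

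Whichever is chosen, use the same resamples for the cost interval, the cost-effectiveness plane and the acceptability curve, and name the cluster explicitly, since the Randomization section speaks of both nurses and practices. Also state how the imputation model reflects practice. That is desirable but secondary.

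The cost is a few sentences in the plan, modest programming and somewhat wider intervals. No further patients or data are needed.

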### Participants

Patients are eligible for this study if they are 18 years or older, are treated for DM2 and/or CHD in primary care, and have subthreshold depressive symptoms (a score of 6 or more on the Patient Health Questionnaire-9, or PHQ-9 [32]) without fulfilling the criteria for major depression according to the Diagnostic and Statistical Manual of Mental Disorders (DSM-IV), as measured with the Mini International Neuropsychiatric Interview (MINI) [33].

Patients are excluded from participation in the study when they have a major depressive disorder; cognitive impairment or dementia; a psychotic or terminal illness; a history of (a) suicide attempt(s); or insufficient Dutch language skills, visual impairments or illiteracy. Also, patients cannot participate when they are pregnant, taking antidepressant medication, or when they have lost a significant other in the past 6 months.

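### The acceptability-curve ceiling ratio is set per recovered patient in a prevention trial, and should be per MDD case prevented and per QALY gained; baseline-utility adjustment is a separate, nearly free improvement

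*Protocol article*

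**What the plan says.** All references are to the protocol article.

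- **Economic evaluation.** "Both a cost-effectiveness analysis and a cost-utility analysis will be performed". The ratio is described as follows: "Incremental cost-effectiveness ratios (ICERs) will be calculated by dividing the difference in mean total costs between the treatment groups, by the difference in mean effects". Acceptability curves are to be drawn over a range of ceiling ratios, which a parenthesis explains as "the willingness to pay for 1 extra recovered patient". The section does not otherwise name the effect unit. It names no covariate and does not exclude adjustment.
- **Participants.** "Patients are excluded from participation in the study when they have a major depressive disorder".
- **Outcomes.** "The primary clinical outcome is the cumulative incidence of DSM-IV major depressive disorder after 12 months". For the utility side, "QALYs will be calculated using the area-under-the-curve method with linear interpolation between time points", and on timing, "All secondary outcomes mentioned above will be administered at baseline, 3, 6, 9 and 12 months after inclusion through web-based questionnaires"; these outcomes include the EQ-5D and the cost questionnaire (TiC-P).
- **Statistical analyses.** The mixed models, including those for quality of life, are adjusted for confounders where needed. A separate sentence promises correction when demographic variables are unevenly distributed between the arms. Neither sentence names baseline EQ-5D or refers to the economic evaluation.
- **Randomization and Recruitment.** Practices are allocated before their patients are recruited, and the GP screens the patient list.

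**The concern.** The main point is the unit. The parenthesis on the ceiling ratio is the only place in the economic section that says what one unit of effect is, and it names an event the trial does not define or count. A decision maker reading the curve needs to know what is being paid for. A depression case averted, a fall in PHQ-9 below the cut-off and a QALY are three different quantities with different willingness-to-pay scales. If the unit stays loose, the effect measure for the cost-effectiveness analysis could be settled after the data are seen. The economic evaluation is the stated aim of the study, so its effect unit is not a side issue.

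The second point concerns precision and protection against imbalance. Baseline utility is one of the points under the QALY curve and also predicts the later points. With about 30 practices, and patients recruited after allocation, the arms may differ in baseline utility by chance or through recruitment. An unadjusted contrast carries part of that difference into the incremental QALYs.

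**Working it through.** **1. The unit, with the sections side by side.**

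| Section | Statement | Implied unit |
|---|---|---|
| Participants | major depression excluded at entry | no one can recover from MDD present at baseline |
| Outcomes | cumulative incidence of MDD at 12 months | case of MDD prevented |
| Outcomes; Economic evaluation | area-under-the-curve QALYs; cost-utility analysis | QALY gained |
| Economic evaluation, parenthesis | ceiling ratio | recovered patient |

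The last row matches none of the others. The Sample size section expects incidence of 30% under usual care and 15% under the intervention. The planned clinical effect is therefore 0.30 − 0.15 = 0.15 cases prevented per patient, or 1/0.15 ≈ 6.7 patients per case prevented. Nothing in the document converts this into a number of recoveries.

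**2. How baseline utility enters the QALY.** The document gives no incremental QALY figure to reproduce. With EQ-5D at 0, 3, 6, 9 and 12 months and linear interpolation, the trapezoid weights are 0.125, 0.25, 0.25, 0.25 and 0.125, which sum to 1. Let d be the baseline difference between arms and b the slope of follow-up utility on baseline utility (assumed). The unadjusted QALY difference then shifts by

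d × (0.125 + 0.875 × b).

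For d = 0.03:

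| b | Shift in QALY difference |
|---|---|
| 0 | 0.03 × 0.125 = 0.004 |
| 0.3 | 0.03 × 0.3875 = 0.012 |
| 0.5 | 0.03 × 0.5625 = 0.017 |
| 0.7 | 0.03 × 0.7375 = 0.022 |

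**3. How large a chance imbalance could be.** From the document: 236 patients, 118 per arm, 30 practices. The ICC of 0.05 is the document's figure for clustering in its sample size calculation; applying it to EQ-5D is an assumption. The EQ-5D SD of 0.20–0.30 is also an assumption.

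- Patients per practice: 236/30 = 7.87.
- Design effect: 1 + (7.87 − 1) × 0.05 = 1.343.
- SE of the baseline difference: SD × √(2 × 1.343/118) = 0.151 × SD.
- For SD 0.20, 0.25 and 0.30: SE = 0.030, 0.038 and 0.045.
- 95% range (1.96 × SE): ±0.059 for SD 0.20, ±0.089 for SD 0.30.

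**4. Effect on the QALY difference.** Take an overall baseline-to-QALY slope of 0.6 (assumed; it corresponds to b = (0.6 − 0.125)/0.875 = 0.54).

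- One SE: 0.6 × 0.030 = 0.018 to 0.6 × 0.045 = 0.027.
- At the 95% limits: 0.6 × 0.059 = 0.035 to 0.6 × 0.089 = 0.053.

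**The case against.** On the unit, the fair reply is that the phrase is a parenthetical gloss on acceptability curves. The ICER sentence speaks only of mean effects, and the Outcomes section makes the intended effects identifiable. Part of this stands. A reader might infer that the ICER denominator itself is wrong, and the document does not show that. Nor can one say that nobody in the trial could recover in any sense: participants enter with a PHQ-9 of 6 or more, and scores may fall below that cut-off. But recovery of that kind is not a defined outcome and is not the primary one. The gloss therefore remains a stated unit that conflicts with other sections, which a fuller document cannot cure by adding detail.

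On baseline utility, the objection is stronger and largely stands. A reader might infer that raw, unadjusted means are prescribed. The text does not say so, because a regression-adjusted contrast is also a difference in means. A condensed article may properly leave covariates to the full protocol or analysis plan. Under randomisation an unadjusted contrast is not wrong in itself: chance imbalance is part of the sampling variability that the bootstrap is meant to show. Recruitment after allocation could add systematic imbalance, but the document gives nothing from which to size it.

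A reader might also infer that imbalance could reverse the sign of the ICER. The document gives no expected QALY gain to set beside the shifts above, so that claim is not supported.

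**Conclusion.** The unit of the ceiling ratio needs correcting. It contradicts the exclusion of MDD at entry and the incidence outcome, and it does not fit the cost-utility analysis. This rests on the document's own text and on no assumption. It is a defect in the definition of the acceptability curves and does not show that the effect side of the ICERs is wrong as a whole.

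Baseline-utility adjustment is a recommended improvement and not the correction of an error. It gains precision, and it protects against an imbalance that the stated rule, limited to demographic variables, would not address. Its size depends on SD, slope and ICC values that the document does not give for EQ-5D. A one-SE imbalance moves the unadjusted QALY difference by about 0.018–0.027 under the assumptions shown. For a fixed imbalance of 0.03, the shift runs from 0.004 to 0.022 as the assumed follow-up slope goes from 0 to 0.7.

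**What to change.** 1. In Economic evaluation, state the effect for each analysis: cases of MDD prevented over 12 months (usual-care incidence minus intervention incidence) for the cost-effectiveness analysis, and QALYs for the cost-utility analysis. Replace the ceiling-ratio gloss with willingness to pay per case of MDD prevented and per QALY gained, with one acceptability curve for each.
2. As an improvement, estimate incremental QALYs by regression with baseline EQ-5D utility as a covariate, and incremental costs with baseline TiC-P costs as a covariate. Fit the two jointly if convenient, for example by seemingly unrelated regression, and refit them within each bootstrap replicate so that the planes and curves reflect the adjusted contrasts. If the full protocol or analysis plan already specifies this, a cross-reference is enough.

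Both are wording changes. Table 1 already schedules EQ-5D and TiC-P at baseline, so no new data, visits or patients are needed.
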